## Abstract

**Introduction:**

Recent evidence suggests that for certain clinical conditions, placebos can improve clinical outcomes even without deception. These so-called *open-label placebos* (OLPs) bear the advantage of a significant lower risk of adverse events and comply with ethical principles. Although premenstrual syndrome (PMS) seems to be considerably susceptible to placebo effects, no study has examined open-OLP responses on PMS.

**Methods and analysis:**

To test the efficacy of OLPs in women suffering from PMS, a clinical randomised controlled trial including two OLP study groups (with and without treatment rationale) was designed to investigate on the effect on PMS. PMS symptoms are monitored on a daily basis via a symptom diary, adverse events are monitored intermittently. The study started in spring 2018 and patients will be included until a maximum of 150 participants are randomised. Besides the primary outcome PMS symptom intensity and interference, an array of further variables is assessed. Multilevel modelling will be used for data analyses.

**Ethics and dissemination:**

Ethics approval was obtained from the Ethics Committee Northwest and Central Switzerland. Results of the main analysis and of secondary analyses will be submitted for publication in peer-reviewed journals.

**Trial registration numbers:**

(1) ClinicalTrials.gov (NCT03547661); (2) Swiss national registration (SNCTP000002809).

Strengths and limitations of this studyThis is the first clinical randomised controlled trial to test an open-label placebo (OLP) intervention in premenstrual syndrome (PMS).Moreover, this trial focuses on OLP responses on a somatic and a psychological outcome.To tackle the challenge of variations in PMS complaints and menstrual cycle lengths within subjects, enrolled women are comprehensively and prospectively screened for PMS and the primary outcomes are also prospectively assessed.We test the effect of a plausible, comprehensive OLP treatment rationale, which may be relevant for a better understanding of effects of treatment rationales in general.Since different definitions of PMS exist, we based our definition on the most highly recommended diagnosis assessment criteria and assessment tools.

## Introduction

Recent evidence suggests that in certain clinical conditions—such as chronic low-back pain,^1^ irritable bowel syndrome,^2^ rhinitis,^3^ and cancer-related fatigue^4^—placebos improve clinical outcomes even without deception. These so-called open-label placebos (OLPs) are prescribed with a plausible scientific treatment rationale, encompassing that placebos are powerful; the body automatically responds to the intake of placebos; a positive attitude towards the intervention can be helpful; and taking the placebo pills faithfully is critical.^1 2 5^ We have shown in a standardised heat pain experiment that the provided treatment rationale is crucial for the elicitation of an OLP response.^6^ To date, no study has examined OLP responses on premenstrual syndrome (PMS), although PMS appears to be susceptible to placebo effects.^7–9^ Moreover, a further analysis of the effect of the OLP treatment rationale can inform about intervention-independent effects of treatment rationales. Hence, we set out to examine OLP responses in PMS and the relevance of a plausible treatment rationale.

## Rationale

PMS entails clinically significant somatic and psychological symptoms in the premenstrual phase of the menstrual cycle, causing substantial distress and functional impairment.^10^ Worldwide, a considerable amount of women of reproductive age are affected with a pooled prevalence of 47.8%.^11^ Subsequently, a myriad of distinctive therapies are prescribed for PMS—including pharmacological and phytopharmaceutic drugs as well as complementary interventions^12^—yet there is limited evidence for some interventions (eg, Chaste tree; anxiolytics) while other empirically validated interventions (eg, selective serotonin reuptake inhibitors, hormonal therapy) show considerable side-effects.^13^

Notably, PMS seems to be highly susceptible to placebo effects: The Royal College of Obstetricians and Gynaecologists alerts to substantial placebo responses in randomised-controlled PMS intervention trials of 36%–43%^7^ and different studies reported considerable placebo effects on PMS.^8 9 14^ Furthermore, PMS offers the opportunity to investigate OLP effects on *both* somatic and psychological symptoms since symptom diaries like the German PMS symptom diary inquire about physical (eg, breast tenderness, headaches, joint and muscle pain) as well as psychological symptoms (eg, depressed mood, hopelessness, irritability). In addition, we are the first to assess the effect of a comprehensive OLP treatment rationale in a clinical population. We hypothesise that first, women obtaining an OLP treatment with a treatment rationale will report less PMS symptom intensity and interference during the course of the intervention and at follow-up, compared to women obtaining an OLP treatment without a treatment rationale. Second, we assume that women receiving an OLP treatment without a treatment rationale will also show a higher decrease in PMS symptom intensity and interference in comparison to the treatment as usual (TAU) group which is not given any of the treatment-specific information that the OLP groups receive nor the rationale for the OLP treatment.

## Objectives

### Primary objectives

The primary objective of this study is to test the effectiveness of an OLP treatment in women suffering from moderate to severe PMS in regard to PMS symptom intensity and interference. Also, we examine whether there is a group difference across time. Moreover, we test whether a comprehensive OLP treatment rationale has an effect on the OLP response compared to omitting the treatment rationale.

### Secondary objectives

To test whether an OLP response is observed for somatic or on psychological symptoms.To assess the effect of the OLP treatment on PMS impact.To evaluate the effect of the OLP intervention on quality of life.To assess whether there is any impact of elevated baseline anxiety or depression levels on the OLP response.To investigate whether there is any effect of the OLP intervention on relationship satisfaction.To assess whether positive attitudes towards complementary medicine are associated with OLP responses.To assess the impact of attitudes towards placebos on the OLP response.To evaluate whether the appraisal of the treatment provider has any effect in regard of the OLP effect.To evaluate the intervention credibility in the two intervention groups.To investigate whether expectancy of relief and desire for relief have an effect on the OLP response.To assess treatment adherence of placebo pill intake.

## Methods and analysis

### Study design

A single-centre, randomised controlled clinical trial of an OLP intervention on women with PMS using a parallel group between-subject design with three study groups: a TAU group; an OLP with a plausible treatment rationale (OLP+) and an OLP without a treatment rationale (OLP−) group. The first participant was enrolled and randomised in August 2018, and the study is expected to be concluded by spring 2020 with the planned inclusion of 150 study participants. The study is being conducted at the Division of Clinical Psychology and Psychotherapy at the Faculty for Psychology of the University of Basel. For an overview, please see box 1. The design of the trial is summarised in figure 1 and all steps and aspects are delineated below (see also table 1 for an overview of the schedule).

**Figure 1 F1:**
[figure not shown]
Study design and flow of participants*.* IC, informed consent; OLP, open-label placebo; PMS, premenstrual syndrome; TAU, treatment as usual.

**Table 1 T1:** Study schedule

Study periods	Screening phase			Intervention phase				
	Preliminary screening of eligibility	Prospective PMS screening	L1 OA	Personal meeting (t0)	L2 OA	Midpoint study contact	L3 OA	Post-treatment study contact & OA (t2)
Visit/contact	Phone/post/online	At home (diary form)	Online	At study site	Online	At study site or phone/Skype	Online	Phone +post-treatment online
Day of menstrual cycle (MC)	−31–−1 day of 1. MC	1. day of 1. MC until end of 1. MC	−5–−1 of 2. MC	1–14 day of 2. MC	−5–−1 of 3. MC	1–14 day of 3. MC	−5–−1 of 4. MC	1–14 day of 4. MC
Menstrual phase	At any point	One whole MC	Luteal	Follicular	Luteal	Follicular	Luteal	Follicular
Time (min)	20	2 daily for 1 MC	10	60	10	15	10	30
Study information/informed consent	x							
Inclusion/exclusion criteria	x	x		x				
Randomisation				x				
Placebo dragée intake in intervention arms				x	x	x	x	
Narrative for OLP+ group				x		x		
**Primary outcome**								
PMS symptom diary		x	x	x	x	x	x	
**Safety variables**			x	x	x		x	x
Suicidality assessment	x			x		x		x
Side-effects assessment						x		x

L, luteal phase; OA, online assessment; OLP, open-label placebo; PMS, premenstrual syndrome.

Box 1Overview about research questions and study design
**Research questions:**
Does an open-label placebo (OLP) intervention alleviate premenstrual syndrome (PMS) symptoms over time?Do participants who receive a comprehensive OLP treatment rationale show a greater OLP response in comparison to participants who do not receive any treatment rationale over time?
**Population:**
Women suffering from a moderate to severe PMS, aged between 18 and 45 with a regular menstrual cycle and no essential comorbidities.
**Intervention groups:**
There are two intervention groups: one OLP with a plausible treatment rationale (OLP+) and an OLP without a plausible treatment rationale (OLP−) group. Both groups obtain openly administered placebo pills, hence two pills per day for 6 weeks.
**Comparison:**
A treatment as usual group without any intervention but the same number of study contacts as the intervention groups and the same study procedures serves as control group.
**Outcome:**
Primary endpoint are PMS symptom intensity and interference measured by means of a PMS symptom diary.

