## Outcome measures: primary, secondary and tertiary

### Primary outcome measures

The German PMS symptom diary consists of 27 symptoms and of three further items assessing interference in different domains (ie, work or school; social activities; relations with others). Usually, a four point Likert scale is employed, however, in line with Endicott *et al*
17 we apply a six point Likert scale to be able to detect subtle changes. We compare changes over time of PMS symptom intensity and interference across three menstrual cycles. The *PMS symptom intensity score* is derived from the first 27 items of the German PMS symptom diary, and the *symptom interference score* is derived from the last three items. With regard to symptom intensity, two additional subscales are calculated by dividing the 27 symptom items into a psychological symptom intensity subscale and a physical symptom intensity subscale score (see secondary outcomes).^17^

Following Kues *et al*
18 and Janda *et al*,^16^ we calculate separate scores for the luteal and follicular phase and consider the difference for our analysis. In more detail, we conservatively consider 7 days prior to menstruation onset as a time slot for the luteal phase and 7 days of the follicular phase, whereas the start of the follicular phase for each participant is calculated using the following formula: (individual cycle duration in days−14)/2=first day of the follicular phase. Subsequently, we calculate the difference score of the means for each menstrual cycle for the respective primary outcome of interest (ie, for PMS symptom intensity or interference). Intensity and interference are considered as marked if rated by participants with at least a 4 (very strong) on a scale from 0 (not at all) to 5 (extreme). Moreover, the item has to be rated with at least a four for at least two consecutive days to be considered as marked. Further, symptoms only are considered as marked symptoms if the respective symptom is not marked in the follicular phase and if it is associated with marked interference in the luteal phase. If a participant has four or more symptoms marked in the luteal phase, also interference of only 1 day is accepted. We are also interested in the trajectory of the symptoms in the intervention groups across the two luteal phases after t0. Hence, we will compare if there are differences of group effects at cycle 2 (C2) and cycle 3 (C3) in contrast to cycle 1 (C1).

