### Sample size

A calculation with a power analysis on the basis of an F-test and an analysis of covariance for three groups, using the statistical software G*Power, indicated a total sample size of 206 participants needed for a power of 0.9 and a total sample size of 158 participants for a power of 0.8 to detect a medium effect size of f=0.25 (equals d=0.5) with an alpha-level of 0.05.

Since we will adopt a multilevel approach which enables more precise estimations, we also conducted a power analysis on a repeated-measures analysis of variance, using G*Power, whereby we are interested in the interaction between time (menstrual cycles, 3 levels) and study groups (3 levels). If the correlation for the outcome among the different time points (1–3 cycles) is assumed to be 0.5, then based on an alpha-level of 0.05, a power of 0.8 and a medium effect size of f=0.25, the required samples size is 36 (12 per group). Accordingly, for the main effect of menstrual cycle, we would need 30 participants (10 per group), and for the main effect of study group we would need 108 participants (36 per group). On this basis, we chose a conservative total sample size of 150 participants (50 per group). It is worth noting that most OLP studies reported effect sizes that are generally higher than d=0.5 (eg, chronic low back pain: d=0.77^1^; irritable bowel syndrome: d=0.79).^2^ However, in another OLP study for patients suffering from major depressive disorder,^5^ the authors reported an effect size of d=0.54 while stating that the study was limited by low statistical power (ie, the findings did not support the hypothesis that OLPs are effective in depression). Since PMS is not only characterised by physical complaints, yet also by psychological symptoms such as depressive mood, and since there is no specific research on OLP effects and effect sizes in PMS, we considered a conservative medium effect size as more appropriate. This resulted in a more conservative sample size.

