### Statistical analysis

For the testing of the primary hypotheses, the daily data from three menstrual cycles of a symptom diary is examined. Because of the hierarchical structure of the data (menstrual cycles as level-1 are nested within participants as level-2) and given our aim to predict post-interventional changes between menstrual cycles as the primary outcome, a multilevel modelling approach will be adopted. Multilevel models take care of the interdependence of the hierarchical data that arises due to the fact that observations within the same individual are typically more similar to each other compared to observations between individuals.^30 31^ Here, we will analyse temporal changes across menstrual cycles of symptom intensity and interference among the different study groups. To compare a TAU group with two intervention groups and to evaluate the effect of the applied treatment rationale, the following linear a priori contrast will be tested for the factor study group: TAU<OLP−<OLP+. Thus, based on published findings,^6^ we expect that the effect of OLP− lies between that of TAU and OLP+. Out statistical model contains menstrual cycle as within-subject factor with three levels (C1, C2 and C3), study group as between-subject factor with three levels (TAU, OLP+ and OLP–), and the interaction between the two factors. In line with recommendations by Fitzmaurice *et al*,^32^ we will treat baseline values (ie, values at C1) as a part of the outcome vector and assume that the means among study groups are equal at baseline since participants are randomised. The model contains the two main effects study group contrast (defined above) and menstrual cycle (temporal effect) plus the interaction between the two. We will be primarily interested in the interaction term as it tests for the differential temporal change between study groups in order as defined in the linear contrast.

Analyses of secondary outcomes are based on the same multilevel model as used for primary outcomes, but will be considered exploratively, thereby not correcting for multiple tests.^33^

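### Two primary outcomes share one undivided alpha of 0.05 with no success rule; if either alone can succeed, the false-positive rate is about 7% to 10%

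*Protocol article*

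**What the plan says.** The protocol article names two primary outcomes in Box 1: "Primary endpoint are PMS symptom intensity and interference measured by means of a PMS symptom diary". The Primary outcome measures section scores them separately, intensity from 27 diary items and interference from three. It forms a luteal-minus-follicular difference for each cycle "for the respective primary outcome of interest (ie, for PMS symptom intensity or interference").

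The Statistical analysis section describes a multilevel model with cycle, study group and their interaction. The groups enter through one ordered contrast (TAU, OLP−, OLP+), and the contrast-by-cycle interaction is the term of main interest. The section gives no significance level for the primary outcomes. On multiplicity it says only that secondary outcomes "will be considered exploratively, thereby not correcting for multiple tests".

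The figure 0.05 appears only in the Sample size section, as an input to power calculations for a single outcome: "to detect a medium effect size of f=0.25 (equals d=0.5) with an alpha-level of 0.05" for the analysis of covariance, and "based on an alpha-level of 0.05" for the repeated-measures calculation.

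The Primary outcome measures section adds a trajectory question: "we will compare if there are differences of group effects at cycle 2 (C2) and cycle 3 (C3) in contrast to cycle 1 (C1"). It does not say whether these comparisons are decision tests.

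**The concern.** With two primary outcomes, the reader needs to know what counts as a positive trial: success on one, on a named one first, or on both. The article does not say. It deals with multiplicity for the secondary outcomes and is silent on the primary pair, where it matters most.

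If the pair is analysed in the natural way, each at 0.05 with either able to support a claim of efficacy, the chance of a false positive primary result exceeds 5%. The safeguard matters more than usual here. Participants know their allocation, as the Trial treatment and study arms section states, and both outcomes are self-rated in the same diary. The choice of success rule also belongs in place before the data are seen.

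**Working it through.** **Inputs from the protocol article**
- Primary outcomes: 2 (Box 1; Primary outcome measures).
- Alpha: 0.05, not divided (Sample size).
- Effect size f = 0.25; three groups, three cycles. Correlation between cycles: "If the correlation for the outcome among the different time points (1–3 cycles) is assumed to be 0.5" (Sample size).
- Planned total: 150, 50 per group (Sample size).

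**Assumed**
- Each primary outcome is tested at 0.05, two-sided. This is inferred from the Sample size section.
- Correlation r between the two test statistics: 0 to 0.9. The article gives no value.

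**Step 1. Reproduce the plan's own figures** (noncentral F, G*Power conventions)
- Interaction: df 4 and 2(N − 3), λ = f²·N·3/(1 − 0.5). At N = 36, λ = 0.0625 × 36 × 3/0.5 = 13.5 and power is 0.82. This is the smallest multiple of three that reaches 0.8. It agrees with "a power of 0.8 and a medium effect size of f=0.25, the required samples size is 36 (12 per group").
- Group main effect: df 2 and N − 3, λ = f²·N·3/(1 + 2 × 0.5). At N = 108, λ = 0.0625 × 108 × 3/2 = 10.125 and power is 0.81, which agrees with the stated 108.
- The stated 30 for the cycle effect and 158 and 206 for the analysis of covariance also reproduce. All of these use the full 0.05 on one outcome.

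**Step 2. Family-wise error if either outcome suffices**

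Independent tests: 1 − (1 − 0.05)² = 1 − 0.9025 = 0.0975.

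Correlated tests: 1 − P(|Z₁| < 1.96 and |Z₂| < 1.96), with (Z₁, Z₂) bivariate normal with correlation r.

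| r | each at 0.05 | each at 0.025 |
|---|---|---|
| 0 | 0.0975 | 0.0494 |
| 0.5 | 0.0907 | 0.0465 |
| 0.7 | 0.0835 | 0.0430 |
| 0.8 | 0.0781 | 0.0402 |
| 0.9 | 0.0704 | 0.0362 |

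These figures are for a test with one degree of freedom per outcome. A simulation with a joint two-degree-of-freedom test per outcome gave almost the same values.

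**Step 3. Family-wise error if both must succeed**

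The chance that both reject cannot exceed the chance that a given true null is rejected, so it is at most 0.05.

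**Step 4. What splitting alpha costs**, each outcome at 0.025
- Sample size for 80% power: interaction 42 instead of 36; group effect 129 instead of 108. Both are below 150.
- Power at N = 150, interaction: λ = 0.0625 × 150 × 3/0.5 = 56.25, power above 0.99.
- Power at N = 150, group effect: λ = 0.0625 × 150 × 3/2 = 14.06, power 0.87, against 0.92 at 0.05.

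**The case against.** **The article never says that one outcome is enough.** The hypotheses in the Rationale section and the primary objective join intensity and interference with 'and'. Read as a joint requirement, that leaves no inflation. This stands as a limit: the 7% to 10% is conditional. But 'and' in a list of outcomes is not a success rule, and nothing in the article excludes a claim on one outcome.

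**No test level is given for the primary outcomes.** This is true, since 0.05 is only a power input. It is nevertheless the only alpha in the article, and the trial was sized with all of it on one outcome.

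**The two scores are likely to be well correlated.** They come from the same diary, the same days and the same women. That favours the lower end of the range: 7.0% to 7.8% at correlations 0.9 to 0.8, about 1.4 to 1.6 times nominal. Doubling is close only near independence.

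**A multiplicity rule may sit in an analysis plan that is not shown.** It may. The absence of detailed testing procedures in an article would be no finding. What counts as success on two named primary outcomes is more basic, and the article does address multiplicity, but only for the secondary outcomes.

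**A stronger reading is tempting.** A reader might infer that C2 and C3 are separate chances of success, giving four primary tests. With a correlation of 0.5 between the cycle contrasts, that would put the error at 16.1%, 14.9% and 12.6% for outcome correlations 0.5, 0.7 and 0.9. The article does not support this. The Statistical analysis section puts the main interest in the interaction, which can be one joint test per outcome. The Primary outcome measures section introduces the trajectory question with 'also', as a supplement. The status of the cycle comparisons should be stated, but inflation from them is not established. Nor do the three groups add tests, because they enter through one ordered contrast.

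**Conclusion.** The point holds in conditional form. The article has two separately scored primary outcomes, one undivided alpha, and no adjustment, order or success rule for the pair. If each is tested at 0.05 and either suffices, the family-wise error is 7.0% to 9.75% for assumed correlations from 0.9 down to 0. If both must succeed, it is at most 5%. It would be wrong to say that the plan's false-positive rate is above 5% without that condition.

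The point should be settled before analysis, because the remedy is cheap. The power figures at 0.025 rest on the plan's f = 0.25 and correlation of 0.5. They also refer to the unstructured interaction used in the Sample size section; the article gives no effect size for the ordered contrast-by-cycle test. On the analysis-of-covariance basis, 150 participants already fall short of the stated 158 at 0.05, so the claim that a split is affordable rests on the repeated-measures basis that the sponsor chose.

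**What to change.** State in the plan, before the data are analysed, how the error is controlled across intensity and interference. Any one of these would do:

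- **Holm, or 0.025 each.** This keeps a stand-alone claim for both outcomes. With a fixed split, power for the group effect falls from 0.92 to 0.87 and stays above 0.99 for the interaction. Holm is never less powerful than the split.
- **A fixed order.** The first outcome is tested at 0.05, and the second at 0.05 only if the first is significant. The first loses no power; the second loses its stand-alone claim. The article does not rank the outcomes, so the order is for the sponsor to justify.
- **Both must succeed, each at 0.05.** This matches the joint wording of the hypotheses. It costs power for the overall claim, by an amount that depends on the unknown correlation.

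Add one sentence naming the single joint contrast-by-cycle interaction test as the decision test for each outcome, with the separate C2 and C3 comparisons as supportive. Give the significance level and sidedness in the Statistical analysis section. The change is to wording only and needs no change to the planned sample size or data collection.
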